### Ethics

This study has been set up in accordance with the principles of the Declaration of Helsinki and Good Clinical Practice guidelines. The medical ethics committee of the University Medical Centre Utrecht approved the study protocol, followed by the Institutional Scientific Boards of each participating centre. Written informed consent is obtained prior to randomization. Structural protocol modifications, including amendments, will be communicated as soon as possible to the medical ethics committee, the trial register, and all involved investigators and participants.

### Statistical analysis

#### Sample size calculation

We determined the sample size based on an assumed cure rate of 92.5% for both groups and a margin of inferiority of 10%, consistent with assumptions in similar UTI trials [5, 12, 13, 16]. Assuming that a difference of 10.0 percentage points or less is irrelevant and with the two-sided alpha set at 0.05, the sample size needed in the two groups is 109. The study has a 80% power to reject the null hypothesis that the clinical cure rate for the study arm (FT) is 10% lower than the cure rate for the standard of care (CPX). Equivalently, the likelihood is 80% that the two-sided 95.0% confidence interval for the difference in clinical cure rates will exclude a 10% difference in favour of standard care. In order to evaluate 109 patients in both treatment arms, taking into account 10% of lost participants for various reasons, 240 subjects will be enrolled in total.

#### Intention to treat and per-protocol analysis

Participants are evaluable if they are randomized and received at least one dose of the study drug, and all will be included in the intention to treat analysis. Analysis of all endpoints will be performed according to the intention-to-treat principle, on which data non-inferiority is based. A per-protocol analysis will be performed for the primary endpoint and the secondary endpoint ‘microbiological cure’ for patients that completed at least 80% of study medicines.

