### Treatment

Participants will be randomized for an intravenous-oral antibiotic switch to either FT 3000 mg every 24 h or CPX 500 mg every 12 h [1]. CPX is chosen for the control group, because most evidence exists for CPX as an oral treatment of FUTI [12, 13]. A double-dummy design is chosen as it is impossible to equalize fosfomycin granules to any form of CPX. An identical placebo will be used for both active substances. All medicines will be manufactured according to Good Manufacturing Principles by the pharmaceutical company Basic Pharma BV, the Netherlands. The duration of total antibiotic therapy is 10 days for all participants, of which 2–5 days empirical intravenous antibiotics and the remaining 5–8 days stepdown therapy with FT or CPX.

FT will be dosed 3 g every 24 h, which is based on a review of the scientific data and expert opinion on the treatment of FUTI and the pharmacokinetics of FT that was available at the moment the study was designed (May 2017). The use of FT every 24 h for more than a single dose was tolerated well in retrospective studies and according to personal off-label use [14]. We do not expect negative effects of accumulation as fosfomycin is registered for intravenous use in dosages as high as 24 g per 24 h [15]. A medication diary needs to be filled by the participant in order to improve medication adherence. All patients receive oral and written information on the trial, including possible risks of participating. Additionally, patients receive a medication folder with instructions for use, contra-indications, interactions and adverse events of both FT and CPX (probable, possible and seldom adverse events). For questions or concerns, participants could contact the local or principle investigator or an independent expert physician.

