### Endpoints

The primary endpoint is clinical cure (resolution of symptoms) 6–10 days post end-of-treatment. Definitions and criteria of primary and secondary endpoints are described in Table 2.

**Table 2 Tab2:** Endpoints, provided with definitions and a time frame

Endpoint	Definition	Time frame
Clinical cure	Alive with reduction of all initial local and systemic FUTI related symptoms and without additional systemic antibiotic therapy for UTI (except antibiotic prophylaxis)	6–10 days post-end of-treatment (PET) + 30–35 days PET
Microbiological cure	Negative urine culture for E.coli (< 10^3^ CFU/ml), phenotypically identifiable to the initial culture (assessment by microbiologist) ^a^	6–10 days PET
Acquired resistance	Resistance to ciprofloxacin, fosfomycin or new ESBL-producing bacteria in phenotypically identical strain	6–10 days PET
Mortality	-Mortality for any reason	Within 30–35 days PET
	-Mortality related to UTI or study medicines	
ICU admission	-ICU admission for any reason	Within 30–35 days PET
	-ICU admission related to UTI or study medicines	
Readmission	-Readmission for any reason	Within 30–35 days PET
	-Readmission related to UTI or study medicines	
Relapse	Development of new symptoms of UTI after previous clinical and microbiological cure with a phenotypically identical strain as isolated during the initial blood or urine (≥10^3^) cultures.	Within 30–35 days PET
Reinfection	Same definition as relapse, but with phenotypically different strains isolated in cultures (urine, ≥10^3^)	Within 30–35 days PET
Additional antibiotic use	Additional systemic antibiotic therapy for UTI (except antibiotic prophylaxis)	Within 30–35 days PET
Length of hospital stay	-Total days of hospital stay	Within 30–35 days PET
	-Total days of ICU stay	
Days of absenteeism	Converted to full work days:	Within 30–35 PET
	-Paid work	
	-Voluntary work	
Adverse events	Possible or probable related to study protocol	Within 30–35 days PET
Early study medicine discontinuation	Early study medicine discontinuation:	–
	-because of intolerance/adverse events	
	-because of clinical failure	
	-because of resolution of symptoms	

^a^Other strains in urine culture will be reported, but do not fall within this definition

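### The 80% completion rule for the per-protocol set removes patients who stop because treatment fails, which weakens that analysis as a check on ITT

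*Protocol article*

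**What the plan says.** Under *Intention to treat and per-protocol analysis*, the protocol article makes ITT decisive: "Analysis of all endpoints will be performed according to the intention-to-treat principle, on which data non-inferiority is based". It then adds a second analysis: "A per-protocol analysis will be performed for the primary endpoint and the secondary endpoint" of microbiological cure. That analysis is "for patients that completed at least 80% of study medicines". No other condition for entering or leaving the set is given.

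Table 2, under *Endpoints*, lists early discontinuation of study medicine as an endpoint with three reasons: intolerance or adverse events, stopping "because of clinical failure", and stopping "because of resolution of symptoms". The same table does not allow clinical cure for a patient given further systemic antibiotics for UTI other than prophylaxis.

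*Treatment* gives the length of the course: "the remaining 5–8 days stepdown therapy with FT or CPX". *Sample size calculation* starts from "an assumed cure rate of 92.5% for both groups" and a 10-point margin.

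**The concern.** A per-protocol set should leave out departures from the protocol, not outcomes. Here, a patient who fails on study medicine, stops it and is switched to another antibiotic is a non-cure in ITT but is absent from the per-protocol set if the switch comes before 80% of the course. The arm with more early failures loses more of them.

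This matters because ITT can lean towards no difference when adherence is poor, and the per-protocol analysis is the only supporting population that the article names for the primary endpoint. A supporting analysis that can discard part of the deficit it should detect gives less reassurance than it appears to. The same set is used for microbiological cure.

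**Working it through.** **The plan's own figure.** With cure of 92.5% in both arms, margin 0.10, two-sided alpha 0.05 and 80% power:

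n per arm = (1.960 + 0.842)² × 2 × 0.925 × 0.075 / 0.10² = 108.9, so 109 as stated. The total of 240 is 218 × 1.1, rounded; that is 120 per arm.

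**Who is removed.** 80% of 5 days is 4.0 days and 80% of 8 days is 6.4 days. Only failures who stop before then leave the set. Failures that appear later, up to the visit 6–10 days after treatment, stay in.

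**Effect on the difference.** Let p be the true cure rate and f the share of failures who stop before 80%. The article does not give f, so it is an assumption shown as a range. With the same f in both arms and no cured patients removed:

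per-protocol cure = p / [p + (1 − p)(1 − f)]

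Take true rates on the margin, 92.5% for ciprofloxacin (CPX) and 82.5% for fosfomycin (FT), with 120 per arm. Expected counts are 111 cures and 9 failures on CPX, and 99 cures and 21 failures on FT. The last column is the simulated share of trials in which the lower limit of the two-sided 95% Wald interval lies above -10 points (400,000 trials per row).

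| f | CPX | FT | Difference (points) | Lower limit above -10 |
|---|---|---|---|---|
| 0 | 111/120 = 92.5% | 99/120 = 82.5% | -10.0 | 3.0% |
| 10% | 111/119.1 = 93.2% | 99/117.9 = 84.0% | -9.2 | 4.5% |
| 25% | 111/117.75 = 94.3% | 99/114.75 = 86.3% | -8.0 | 8.9% |
| 50% | 111/115.5 = 96.1% | 99/109.5 = 90.4% | -5.7 | 28.4% |

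**Cured patients are removed too.** Let g be the share of cured patients who stop before 80%, because of intolerance or because they feel well:

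per-protocol cure = p(1 − g) / [p(1 − g) + (1 − p)(1 − f)]

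- f = g = 10% in both arms: the factor cancels. The difference is -10.0, and about 3% of trials clear the margin.
- f = 25%, g = 10% in both arms: 93.7% v 85.0%, a difference of -8.7; about 6% clear the margin.
- f = 10% in both arms, g = 5% on CPX and 15% on FT, 109 per arm: 0.87875/0.94625 = 92.9% v 0.70125/0.85875 = 81.7%, a difference of -11.2; 1.7% clear the margin.

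**ITT and per-protocol together.** In the f = 50% row, ITT passes in about 3% of trials and both analyses pass in about 2.8%. In about 26%, per-protocol passes while ITT does not.

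**The case against.** **The trial's decision does not move.** A reader might take the 28% as a false-positive rate for the trial. The article does not support that: non-inferiority is judged on ITT, and per-protocol carries no decision rule. At the margin the two analyses agree on a false pass in only about 3% of trials; the usual result of the distortion is visible disagreement, with no claim made. This stands in full.

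**The direction is not fixed.** A reader might also infer that the set always leans towards non-inferiority. It does so only if failures are removed more often than cures. Table 2 foresees stops for intolerance and for resolved symptoms, and the *Discussion* reports fewer diarrhoea-free days with daily fosfomycin in healthy volunteers. More intolerance stops on FT could turn the bias against it, as the -11.2 case shows. This stands, but it is no defence of the rule: it describes a second exclusion that can depend on outcome.

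**Large values of f may be unlikely.** Patients enter after at least 48 hours of appropriate intravenous treatment, when judged fit for an oral switch, and cure is assessed well after treatment ends. Few failures may fall in the first 4.0 to 6.4 days. That is fair. The 10% row deserves as much attention as the 50% row, and the article cannot settle which is closer.

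**An article condenses its protocol.** Fine detail on analysis sets is often left to the SAP. Here, however, the article states a membership rule, and followed as written that rule removes on-treatment failures. An exception elsewhere would change the stated rule, not merely fill it in.

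**Conclusion.** The point holds as a defect in a supporting analysis. Membership of the per-protocol set depends on the outcome, because patients who stop early for clinical failure are dropped instead of counted as non-cures. With no cured patients removed and true rates on the margin, the deficit of 10.0 points appears as 9.2, 8.0 or 5.7 when 10%, 25% or 50% of failures are removed. These sizes rest on assumed shares, equal in both arms. Removal of cured patients can cancel or reverse the shift, so neither its size nor its sign can be fixed from the article. The ITT-based conclusion on non-inferiority is not at risk. What is weakened is the per-protocol analysis, for clinical and microbiological cure, as a check on it.

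**What to change.** Before unblinding, define the per-protocol set as:

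- patients who took at least 80% of study medicine; plus
- patients who stopped it, or received additional systemic antibiotics for UTI, because of clinical failure, whatever share they had taken. These count as clinical non-cures.

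Use the same set for microbiological cure. Report the analysis as supportive alongside ITT, and discuss any disagreement. It should not become co-primary: the trial is powered for one comparison at 109 per arm, and a second required test on a smaller set would cost power.

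The cost is a few sentences. The reason for discontinuation and additional antibiotic use are already Table 2 endpoints, so no new data are needed. Per-protocol cure rates become slightly less favourable. The new set is not perfectly neutral either, since it keeps early-stopping failures and still drops early-stopping cures. If all failures are kept and 10% of cures are dropped in both arms, the rates are 0.8325/0.9075 = 91.7% v 0.7425/0.9175 = 80.9%, a difference of -10.8 instead of -10.0. In that example the remaining shift is small and does not favour non-inferiority.

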#### Statistical methods

For the primary endpoint, the difference between the study arm and standard of care (*p* < 0.05) will be calculated with a two-sided Z-score for proportions. Secondary outcomes will be analysed using the following tests: two-tailed Z-score for proportions (p < 0.05), t-test, chi-square, logistic regression, when appropriate.

Linear and logistic regression will be used to identify associations between patient, disease and treatment characteristics) with both study arms with regard to the primary and secondary endpoints. Clinical cure 6–10 and 30–35 days post-treatment in specific subgroups will be investigated in exploratory analyses, based on host or disease characteristics, e.g. age, BMI, Charlson index, use of immunosuppressive drugs, presence of host factors, presence of a short term indwelling catheter, creatinine clearance, diabetes mellitus, days of empirical intravenous antibiotics, class of empirical intravenous antibiotics, and concomitant bacteraemia.

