**Methods:**

The FORECAST study (Fosfomycin Randomized controlled trial for *E.coli* urinary tract infections as Alternative Stepdown Treatment) is a randomized, double-blind, double-dummy, non-inferiority trial in which 240 patients will be randomly allocated to a stepdown treatment with FT or ciprofloxacin (standard of care) for FUTI, caused by *Escherichia coli* with in vitro susceptibility to both antibiotics*.* The study population consists of consenting female patients (≥18 years) with community acquired *E. coli* FUTI. After intravenous antibiotic treatment during at least 48 (but less than 120) hours, and if eligibility criteria for iv-oral switch are met, patients receive either FT (3 g every 24 h) or ciprofloxacin (500 mg every 12 h) for a total antibiotic duration of 10 days. The primary endpoint is clinical cure (resolution of symptoms) 6–10 days post-treatment. Secondary endpoints are microbiological cure 6–10 days post-treatment, clinical cure, mortality, ICU admittance, relapse, reinfection, readmission, additional antibiotic use for UTI, early study discontinuation, adverse events, days of hospitalization and days of absenteeism within 30–35 days post-treatment. The sample size is based on achieving non-inferiority on the primary endpoint, applying a non-inferiority margin of 10%, a two-sided *p*-value of < 0.05 and a power of 80%.

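### The Statistical methods section states the primary test as a two-sided Z-score at p<0.05 without the 10-point margin, which does not match the non-inferiority criterion behind the sample size

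*Protocol article*

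**What the plan says.** The protocol article describes the primary comparison in two places.

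- **Statistical methods** says how the endpoint will be analysed: the difference between the two arms ("p* < 0.05) will be calculated with a two-sided Z-score for proportions". The next sentence covers the rest: "Secondary outcomes will be analysed using the following tests: two-tailed Z-score for proportions (p < 0.05), t-test, chi-square, logistic regression, when appropriate".
- **Sample size calculation** assumes "an assumed cure rate of 92.5% for both groups and a margin of inferiority of 10" percent, and states that "with the two-sided alpha set at 0.05, the sample size needed in the two groups is 109". It claims "80% power to reject the null hypothesis that the clinical cure rate for the study arm (FT) is 10% lower" than under ciprofloxacin (CPX). As the equivalent statement it gives an 80% likelihood that the "two-sided 95.0% confidence interval for the difference in clinical cure rates will exclude a 10% difference in favour of standard care".

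The Methods part of the abstract puts margin and p-value together: "applying a non-inferiority margin of 10%, a two-sided *p*-value of < 0.05 and a power of 80" percent. The section on intention-to-treat and per-protocol analysis says that non-inferiority rests on the intention-to-treat data, but gives no decision rule.

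**The concern.** The sentence in Statistical methods is the article's only statement of how the primary endpoint will be tested. It names no null value, and a two-sided Z-score for a difference in proportions is ordinarily taken against zero. That reading is strengthened by the near-identical wording for secondary outcomes, for which no margin exists.

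A test of zero difference answers another question. A p-value of 0.05 or more does not show that FT is at most 10 points worse. A p-value below 0.05 does not, taken alone, place the difference on either side of -10 points. Only significance in FT's favour would bring non-inferiority with it, and that is rare when the arms are equal.

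At stake is which rule decides the trial. With two rules in one article, an analyst could defend either after seeing the data. The futility rule at 100 participants (interim-analysis paragraph under Safety) also refers to the chance of finding non-inferiority at the end, and so depends on the final success rule.

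**Working it through.** **Inputs.** From Sample size calculation: cure 92.5% in both arms, margin 10 points, two-sided alpha 0.05 (one-sided 0.025 against the margin), power 80%, 109 evaluable per arm, 240 enrolled (120 per arm at 1:1). From Statistical methods: two-sided Z-score at p<0.05. My assumptions: pooled variance for the equality Z, and an unpooled (Wald) interval for the margin rule, since the article names neither.

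**Step 1. Reproduce the stated sample size.** With unpooled variance,

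n = 2p(1-p)(1.960 + 0.842)² / 0.10² = 0.13875 × 7.849 / 0.01 = 108.9, so 109 per arm.

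Power at 109: SE = √(0.13875/109) = 0.0357, and Φ(0.10/0.0357 - 1.960) = 80.0%. The plan's figure reproduces as a margin-based design.

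**Step 2. Ask what an equality test would need.** For 92.5% v 82.5% with 80% power,

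n = [1.960√(2 × 0.875 × 0.125) + 0.842√(0.069375 + 0.144375)]² / 0.10² = (0.917 + 0.389)² / 0.01 ≈ 171 per arm.

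So 109 belongs to the criterion in Sample size calculation. At 109 per arm the equality test has only 61% power by formula (63% by enumeration) to detect a 10-point deficit.

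**Step 3. Compare the two rules.** All outcomes of two binomials were enumerated.

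| True cure, FT v CPX | Event | 109 per arm | 120 per arm |
|---|---|---|---|
| 92.5% v 92.5% | 95% CI lower limit above -10 points | 80.3% | 84.4% |
| 92.5% v 92.5% | Equality test significant in favour of FT | 2.6% | 2.7% |
| 92.5% v 92.5% | Equality test non-significant, yet margin rule failed | 17.1% | 12.9% |
| 82.5% v 92.5% | 95% CI lower limit above -10 points (false claim) | 3.0% | 3.0% |
| 82.5% v 92.5% | Equality test non-significant | 37.3% | 33.8% |

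**Step 4. Worked results, 109 per arm.**

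- FT 96/109 (88.1%) v CPX 101/109 (92.7%): difference -4.6 points. Z = -0.0459/0.0400 = -1.15, p = 0.25. The 95% CI is -4.6 ± 1.96 × 3.98, or -12.4 to +3.2. Non-significant, and non-inferiority not shown.
- FT 92/109 v CPX 101/109: p = 0.056, with a lower limit of -16.6 points. Non-significant, and well past the margin.
- FT 99/109 v CPX 101/109: p = 0.62, with a lower limit of -9.1 points. Non-significant, and non-inferior.

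All three have p above 0.05, and only the last meets the margin.

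**Step 5. Effect of the interval method.** With a score test against the margin (Farrington-Manning), enumeration gives a one-sided error of 2.5% at 109 per arm and 2.4% at 120. Power is 75.5% and 79.0%. The unpooled interval matches the stated 109 and 80%, at an actual error of 3.0% against the nominal 2.5%.

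**The case against.** The strongest reply is that the article already contains the right rule. Sample size calculation, under the same Statistical analysis heading, states the margin-shifted null and the equivalent 95% interval criterion. The abstract ties the margin to the p-value, and the objective, the analysis-set section and the futility rule all speak of non-inferiority. Statistical methods names no null, so its Z-score may be loose wording for a Z taken against -10 points. The article also condenses a fuller protocol.

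Much of this stands. A reader might infer that the trial ignores its margin and has no way to support its claim. The article does not bear that out: margin, direction, alpha and null are all stated. A reader might also take 37% as the trial's false-claim rate. It is not, because nowhere does the article say that p≥0.05 will count as non-inferiority. Nor is a score interval required: the choice of interval method is commonly left to the analysis plan, and this one lowers power.

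What does not stand is that nothing needs changing. The interval criterion appears only as a power statement that justifies the sample size. The sentence that says what will be done leaves it out and shares its wording with tests that have no margin. Nor is this an omission left to the analysis plan: the article does state the primary test, and in its plain reading that test does not fit the stated null.

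**Conclusion.** The point holds as an unreconciled statement of the primary analysis. The design, margin and sample size are not at fault: 109 per arm reproduces exactly.

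Read plainly, the test in Statistical methods is one of zero difference, and it can disagree with the criterion the trial was powered for. The unconditional size of the mismatch is the 17% of trials that, with 92.5% cure in both arms and 109 per arm, are non-significant and still fail the margin rule. The 37% against 3% contrast at a true 10-point deficit is conditional on reading non-significance as non-inferiority; it shows why that reading must be closed off. These figures rest on the planned cure rates, a pooled equality Z and an unpooled interval. At 120 per arm they are 13%, and 34% against 3%.

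**What to change.** Replace the primary-endpoint sentence in Statistical methods with:

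> The difference in clinical cure (FT minus CPX) will be estimated with a two-sided 95% confidence interval; non-inferiority is concluded if the lower limit is above -10 percentage points.

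Make any Z-test of equality secondary, to be read only after non-inferiority is met. Name the interval method where the analysis is specified in full.

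The cost is one sentence, settled before the final data are unblinded. With the simple unpooled interval the 109 per arm and 80% power stand. A score interval is optional; if it is chosen, restate the power (about 76% at 109 per arm, 79% at 120).
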